## Abstract

**Background:**

Nowadays, because of the increasing incidence, the prevention and control of myopia has become an urgent issue. In China, auricular acupressure has been commonly used in the clinical treatment of myopia in children, but the exact effectiveness remains unproven. The purpose of this trial is to observe the efficacy of auricular acupressure in myopia prevention and control, as well as its effect on the choroidal and retinal thickness.

**Method/design:**

A total of 480 subjects at 8–9 years old will be randomized in a 1:1 ratio to an intervention group versus a control group. The intervention group will receive auricular acupressure for 12 months, while the control group will be taken as a blank control. The primary and secondary outcomes will be measured at baseline, and again at 3, 6, 9, and 12 months after recruitment. The myopia incidence (spherical equivalent ≤ − 0.50 D) and the mean change of spherical equivalent will be taken as the primary variables; the secondary outcome measures include axial length, uncorrected visual acuity, and choroidal and retinal thickness.

**Discussion:**

This trial aims to evaluate the effectiveness of auricular acupressure for myopia prevention and control with objective evidence and to preliminarily explore the plausible mechanism and provide reference for adopting this approach to retard the onset and control the progression of myopia.

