Currently, the interventions for myopia are under four categories [12]: optical, pharmacological, surgical, and environmental (behavioral). Increased time spent outdoors is the only intervention known to reduce the onset of myopia, but it requires at least 14 h to neutralize the risk of parental myopia [13], which is nearly a mission impossible considering the intense education in Chinese children. Because both, myopia onset and myopia progression, depend on or are associated with axial elongation, some interventions known to slow progression can also be applied to pre-myopes. Orthokeratology treatment is limited to children over 8 years old in China and its efficacy seems negatively correlated with the age of the Chinese children [14], so younger children may not benefit from it and its related infection risk also cannot be ignored. In recent years, the effect of 0.01% atropine eye drops in slowing myopic progression has been shown in different studies from various countries [15–17], but its effect on axial length elongation remains controversial [15, 16]. A higher concentration atropine has been intended for children who showed poor response to 0.01% atropine. However, greater accommodative amplitude loss and pupil dilation [18] will be induced, not favorable in terms of long-term safety. Surgical interventions such as posterior scleral reinforcement aim at stabilizing highly myopic eyes, which are not common strategies for myopia prevention. Yet, no ideal therapy is available for preventing the onset of myopia in China.

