Acupuncture-moxibustion is one major part of traditional Chinese medicine (TCM). Acupuncture treatment can produce certain effect in reducing myopia in kids [19]. Nevertheless, acupuncture requires high operation skills and most children are afraid of needling, which make it difficult for large-scale promotion. As another acupuncture-moxibustion treatment branch, auricular acupressure has been commonly used to treat ocular diseases, especially myopia in children, because it is simple-to-operate, non-invasive, and less likely to cause side effects [20]. Previous studies [21–23] have shown that auricular acupressure can effectively slow down the progression of myopia, but these studies are rather limited by poor research methods, such as small sample size and short intervention time, which have weakened this conclusion. To today, there is no high-quality research studying how well auricular acupressure works to prevent myopia or slow down its progression, and thus it is of great clinical value to conduct such a study.

Axial elongation is one of the main anatomical changes with the increase of diopter. The stretching of axial elongation will make the choroid and retina thinner [24, 25]. Retina serves as the center in refractive regulation, in which photoreceptors, nerve fibers, and other structures are closely related to the onset and development of myopia [26]. Choroid provides oxygen and nutrition to retina and adapts the retina to the focal plane of the eye by changing its thickness [27, 28]. Moreover, thicker choroid will hinder the transfer of metabolic growth factors to sclera, slowing down the synthesis of scleral matrix and the axial growth [29]. In addition, choroid responds faster than the eye’s axis. Therefore, observing choroidal thickness is helpful to observe the development of early-stage myopia and explore its mechanism [30, 31].

This trial is supposed to evaluate the effectiveness of auricular acupressure in the prevention and control of myopia in children by observing the myopia incidence (MI), changes in spherical equivalent (SE), axial length, and uncorrected visual acuity and to explore the pertinent action mechanism by detecting the changes in choroidal and retinal thickness. The results of this study will provide clinical evidence for using auricular acupoints to prevent and control myopia in children.

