### Subjects

#### Inclusion criteria

Those who are willing to participate in the trial and meet the following conditions will be included: ages 8 to 9 years old; SE (after cycloplegia), − 0.5 D to + 0.5 D; uncorrected visual acuity ≥ 0.8; corneal curvature, 40 D–46 D; with good compliance; and the subject and his/her guardians signed the informed consent form.

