#### Primary outcome measures

The primary outcome measures include MI and SE.

The measurement of SE will be carried out with Nidek ARK-1 refractometer produced by Nidek, Japan. Before measurement, the subjects were given one drop of 0.5% proparacaine hydrochloride eye drops (Alcaine), one drop of 1% cyclopentolate hydrochloride eye drops (CYCLOGYL) 1 min later, and one drop of 1% cyclopentolate hydrochloride eye drops (CYCLOGYL) 5 min later, to induce cycloplegia, getting ready for automatic optometry 30 min later. The measurement will be performed three times successively. Make sure that the maximum-minimum difference in the spherical and cylindrical diopters should be no more than 0.25 D, respectively, and the average value of the three measurement results will be recorded. The SE is defined as spherical diopter plus 1/2 cylindrical diopter. According to existing reports and clinical routines [35], we define myopia as SE ≤ − 0.50 D.

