Differential diagnosis and treatment is one unique characteristic in TCM. In the actual diagnosis and treatment process, doctors will carry out individually tailored treatment based on each patient’s own situation. Therefore, how to select the acupoints in clinical acupuncture-moxibustion trials is a problem faced by acupuncture researchers worldwide. In this protocol, same auricular acupoint prescription will be used in all subjects in the intervention group. This fixed prescription is based on the comprehensive consideration of the feasibility and quality control of the study, and it is suitable for the prevention and control of various types of myopia. In TCM theory, myopia is mainly due to imbalanced function of the heart, liver, spleen, and kidney, leading to a lack of source transforming into essence and qi, in which the eyes cannot obtain enough nutrition, so that the physiological function of the eyes is damaged [38, 39]. In the auricular acupoint prescription, eye (LO_5_) is selected according to the disease location, and stimulating this point can unblock qi and blood flow in the eyes; since the liver and kidney share the same origin according to TCM theory, liver (CO_12_) and kidney (CO_10_) can be used together to regulate and reinforce the two organs, nourish yin and supplement essence, maintain blood and brighten the eyes; heart (CO_15_) can adjust heart qi and soothe the mind, so that qi and blood will be sufficient to go up and nourish the eyes; spleen (CO_13_) can strengthen the spleen function and supplement qi, and help with the production and transformation of qi and blood, so that the essence and qi can travel upward to nourish the eyes; shenmen (TF_4_) functions to sedate and calm the mind, so it can be used together with liver (CO_12_), kidney (CO_10_), heart (CO_15_), and spleen (CO_13_) to strengthen the effect on mind. The combination of these acupoints work to regulate and tonify the internal organs, conserve blood and replenish qi, activate blood circulation, and dredge collaterals, so that qi and blood can fully nourish the eyes to improve vision.

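### The objective extends to controlling myopia progression, but no enrolled child is more myopic than the threshold, so SE and axial length can show only onset, myopic shift and elongation within the entry range

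*Protocol article*

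**What the plan says.** **Aim.** The abstract gives the purpose as efficacy in myopia prevention and control. Its Discussion paragraph says the trial will serve as a reference for using the approach to "retard the onset and control the progression of myopia". The Research background motivates the study by the lack of high-quality research on "how well auricular acupressure works to prevent myopia or slow down its progression", and states the aim as to "evaluate the effectiveness of auricular acupressure in the prevention and control of myopia in children", judged by myopia incidence, SE change, axial length and uncorrected visual acuity.

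**Population.** The Inclusion criteria require age 8 to 9 years, "SE (after cycloplegia), − 0.5 D to + 0.5 D" and uncorrected visual acuity of at least 0.8. The Exclusion criteria remove children who have used atropine, orthokeratology or other myopia control methods.

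**Case definition.** Under Primary outcome measures, "we define myopia as SE ≤ − 0.50 D". The threshold value itself counts as myopia.

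**Analysis.** Incidence and SE are both primary. Under Statistical analysis, changes in SE and axial length are compared between arms by GEE in a modified intention-to-treat set. No analysis restricted to myopic eyes, or to children who become myopic, is stated. The sample size rests on incidence alone.

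**The concern.** Preventing onset and slowing progression are different claims about different children. The first concerns children who are not yet myopic; the second concerns children who are. The aim covers both, but the entry range admits only the first group, apart from any child exactly at −0.50 D.

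SE is a primary variable analysed in everyone, so a significant treatment effect on SE or axial length is a plausible headline result. Under the present wording a reader could take it as evidence for treating children who already have myopia, a group the trial does not randomise. The planned comparison would still be valid for the children enrolled. What is at stake is the population and the claim to which its result is attached.

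**Working it through.** **1. Entry range against case definition.**

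| SE at entry | Eligible? | Myopic by the protocol's definition? |
|---|---|---|
| below −0.50 D | no | yes |
| exactly −0.50 D | yes | yes |
| above −0.50 D to +0.50 D | yes | no |

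No enrolled child lies beyond the threshold. At exactly −0.50 D the two sections overlap: such a child is eligible and already meets the incidence endpoint at baseline. The document gives no SE distribution, so the number of these children cannot be estimated.

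**2. What the SE comparison estimates.** GEE on all analysed children compares mean SE change in a group that starts between −0.50 D and +0.50 D. That is myopic shift.

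**3. The plan's own sample size.** Inputs from Sample size: 8.41% per year (intervention), 17.65% per year (control), α 0.05, power 0.80, 1:1 allocation, 15% dropout. With the two-sided normal value (1.960) in the printed formula:

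n = (1.960 + 0.842)² / (0.0841 − 0.1765)² × [0.0841 × 0.9159 + 0.1765 × 0.8235] = 204.4 per group

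The stated figure is 204. Recruitment is 408 / 0.85 = 480, as stated. The size reproduces, and progression plays no part in it.

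**4. Children who become myopic on study, at these rates.**

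| Followed per arm | Intervention | Control | Total | Share |
|---|---|---|---|---|
| 240 (no dropout) | 240 × 0.0841 = 20.2 | 240 × 0.1765 = 42.4 | 62.5 of 480 | 13.0% |
| 204 (evaluable) | 204 × 0.0841 = 17.2 | 204 × 0.1765 = 36.0 | 53.2 of 408 | 13.0% |

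About 87% of children would supply SE data without ever reaching the threshold. The rates are taken from an outdoor-activity study and may not fit this entry range. If both were doubled, the share would be 2 × 13.0% = 26%, still a minority.

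**5. What a comparison within that subset could show.** The plan states no such comparison; this only sizes it. The detectable difference at 80% power and two-sided 0.05 is (1.960 + 0.842) × √(1/n₁ + 1/n₂) in SD units:

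- 204 v 204: 2.802 × √(2/204) = 0.28 SD
- 17 v 36: 2.802 × √(1/17 + 1/36) = 0.82 SD

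The subset is formed after randomisation and, if the intervention works, formed differently in the two arms. Even a large difference would not be a randomised contrast.

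**6. Time left after onset.** The document does not say when onset will be detected. A child first meeting the definition at month 3, 6, 9 or 12 has 9, 6, 3 or 0 months of follow-up left. If detection were spread evenly (an assumption), the mean would be (9 + 6 + 3 + 0)/4 = 4.5 months; the possible range is 0 to 9.

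**The case against.** The strongest reply is that the protocol does not formally set progression in myopic children as an objective. The explicit aim is prevention and control, the abstract speaks only of providing reference, and the outcome is named neutrally as mean SE change. This stands in part: the wording is softer than a formal objective. But the same sentence of the abstract names progression as something the trial will inform, and the background motivates the study partly by the gap on progression.

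A second reply is that onset and progression share a mechanism. The Research background links both to axial elongation and argues that "some interventions known to slow progression can also be applied to pre-myopes". SE and axial length are measured in every child, so the 87% who stay below the threshold give some indirect information. That is fair, and it would be too strong to say that they contribute nothing. But the argument carries treatments from progression to pre-myopes. Reading this trial as evidence on progression needs the reverse step, for which the document gives no support.

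Three stronger readings might be inferred, and the text does not bear them out:

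- **That progression cannot be examined at all.** Threshold children and those who become myopic can progress within 12 months. What is missing is a stated analysis and a valid randomised comparison.
- **That a positive SE result will be reported as progression control.** No section says so. The wording creates a risk of that reading, not a documented intention.
- **That the trial plans to conclude for many forms of myopia.** The main Discussion does say of the fixed acupoint prescription that "it is suitable for the prevention and control of various types of myopia". There it explains why one prescription is used for all subjects; it is treatment rationale, not a planned conclusion.

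**Conclusion.** The concern holds as a mismatch between the wording of the aim and the enrolled population. Setting the entry range beside the case definition is enough to show it; no assumption about effect size is needed. The randomised SE and axial length comparisons answer a question about shift and elongation in children at or above −0.50 D, and give no direct randomised evidence on slowing established myopia.

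The 13% who become myopic on study depends on the protocol's borrowed incidence rates. The 4.5 months after onset depends on an assumed even spread, and the conclusion does not need it.

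The −0.50 D overlap is a small but real inconsistency. It prevents the population from being called non-myopic at baseline without qualification. It also leaves open whether a threshold child counts as an incident case.

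Population, endpoints, sample size and the GEE analysis need no change on this account. The change is worth making because SE is a primary variable and its interpretation depends on this wording.

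**What to change.** 1. In the abstract (Background and Discussion paragraphs) and the aim in the Research background, restate the objective as onset of myopia, and myopic shift and axial elongation, in children aged 8–9 within the entry SE range. Attach the same interpretation to the SE and axial length results.
2. Drop control of myopia progression from what the trial may conclude.
3. If SE change after on-study onset is looked at, label it descriptive, because the subset is selected after randomisation.
4. Reconcile the Inclusion criteria with the myopia definition at −0.50 D, so that the population can correctly be called non-myopic at baseline.

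Items 1 to 3 change wording only and need no new participants, visits or planned analyses. Item 4 touches one boundary value. The downside is a narrower claim.

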**Trial registration:**

Chinese Clinical Trial Registry ChiCTR2000038456. Registered on September 23, 2020.

**Supplementary Information:**

The online version contains supplementary material available at 10.1186/s13063-021-05334-1.

## Research background

Myopia is a condition in which the resting eye focuses the parallel rays in front of the retina due to excessive axial elongation or refraction. Large-scale epidemiological survey conducted in China indicated that the prevalence of myopia is now 70–85% in students at the age of 17 to 18 [1–3], being extremely higher than that of 25.7% seen before 2001 [4]. In East Asia, myopia is found to progress rapidly, especially in school children. Although East Asian countries have the highest prevalence, an increasing myopic shift is also observed in Australia [5], Northern Ireland [6, 7], New Delhi [8, 9], and other regions of the world. By 2050, it is estimated that nearly 5 billion people will be affected by myopia at the global scale [10]. Hence, the rapidly increasing prevalence of myopia is of worldwide concern in the twenty-first century. Early-onset myopia may progress to high myopia, which predisposes the patients to a series of sight-threatening pathological consequences, such as retinal detachment and macular degeneration [11]. Therefore, a strategy to postpone the age of myopia onset has become an important issue to be solved urgently.

Currently, the interventions for myopia are under four categories [12]: optical, pharmacological, surgical, and environmental (behavioral). Increased time spent outdoors is the only intervention known to reduce the onset of myopia, but it requires at least 14 h to neutralize the risk of parental myopia [13], which is nearly a mission impossible considering the intense education in Chinese children. Because both, myopia onset and myopia progression, depend on or are associated with axial elongation, some interventions known to slow progression can also be applied to pre-myopes. Orthokeratology treatment is limited to children over 8 years old in China and its efficacy seems negatively correlated with the age of the Chinese children [14], so younger children may not benefit from it and its related infection risk also cannot be ignored. In recent years, the effect of 0.01% atropine eye drops in slowing myopic progression has been shown in different studies from various countries [15–17], but its effect on axial length elongation remains controversial [15, 16]. A higher concentration atropine has been intended for children who showed poor response to 0.01% atropine. However, greater accommodative amplitude loss and pupil dilation [18] will be induced, not favorable in terms of long-term safety. Surgical interventions such as posterior scleral reinforcement aim at stabilizing highly myopic eyes, which are not common strategies for myopia prevention. Yet, no ideal therapy is available for preventing the onset of myopia in China.

Acupuncture-moxibustion is one major part of traditional Chinese medicine (TCM). Acupuncture treatment can produce certain effect in reducing myopia in kids [19]. Nevertheless, acupuncture requires high operation skills and most children are afraid of needling, which make it difficult for large-scale promotion. As another acupuncture-moxibustion treatment branch, auricular acupressure has been commonly used to treat ocular diseases, especially myopia in children, because it is simple-to-operate, non-invasive, and less likely to cause side effects [20]. Previous studies [21–23] have shown that auricular acupressure can effectively slow down the progression of myopia, but these studies are rather limited by poor research methods, such as small sample size and short intervention time, which have weakened this conclusion. To today, there is no high-quality research studying how well auricular acupressure works to prevent myopia or slow down its progression, and thus it is of great clinical value to conduct such a study.

Axial elongation is one of the main anatomical changes with the increase of diopter. The stretching of axial elongation will make the choroid and retina thinner [24, 25]. Retina serves as the center in refractive regulation, in which photoreceptors, nerve fibers, and other structures are closely related to the onset and development of myopia [26]. Choroid provides oxygen and nutrition to retina and adapts the retina to the focal plane of the eye by changing its thickness [27, 28]. Moreover, thicker choroid will hinder the transfer of metabolic growth factors to sclera, slowing down the synthesis of scleral matrix and the axial growth [29]. In addition, choroid responds faster than the eye’s axis. Therefore, observing choroidal thickness is helpful to observe the development of early-stage myopia and explore its mechanism [30, 31].

This trial is supposed to evaluate the effectiveness of auricular acupressure in the prevention and control of myopia in children by observing the myopia incidence (MI), changes in spherical equivalent (SE), axial length, and uncorrected visual acuity and to explore the pertinent action mechanism by detecting the changes in choroidal and retinal thickness. The results of this study will provide clinical evidence for using auricular acupoints to prevent and control myopia in children.

## Method/design

### Design of the trial

This parallel, randomized, blank controlled prospective clinical trial will be carried out in the Eye and ENT Hospital of Fudan University and Shuguang Hospital Affiliated to Shanghai University of Traditional Chinese Medicine, two top-rank hospitals in China. The subjects will be randomized in a 1:1 ratio to an intervention group versus a control group. The intervention group will receive auricular acupressure for 12 months, while the control group will not receive any interventions. A series of optical examinations will be performed at baseline, and 3, 6, 9, and 12 months after recruitment. The whole flow of the trial is illustrated in Figure S1 and the schedule is shown in Table 1. During the study, the subjects will be asked to keep a journal to record their compliance. The research staff will inform each subject of the details of the study before intervention, and all the subjects and their guardians will provide written consent before the treatment starts and they will all be given sufficient time to reach the final decision.

**Table 1 Tab1:** Schedule of treatment assessments and data collection

	Enrollment and baseline	Study period					
		Allocation	Post-allocation				Close-out
Time point (month)	-	0	3	6	9	12	
Informed consent	×						
Inclusion/exclusion	×						
General information	×						
Random allocation		×					
Intervention (auricular acupressure)		×	×	×	×	×	
SE (after cycloplegia)	×		×	×	×	×	
Axial length	×		×	×	×	×	
Uncorrected visual acuity	×		×	×	×	×	
Corneal curvature	×						
Retina thickness	×		×	×	×	×	
Choroid thickness	×		×	×	×	×	
Outdoor light exposure			×	×	×	×	
Near work			×	×	×	×	
Concomitant medication	×		×	×	×	×	
Adverse events and other unintended effects			×	×	×	×	
Compliance			×	×	×	×	
Completion summary							×

This trial will follow the Declaration of Helsinki (version 2013) and has been approved by the Ethics Committee of Shuguang Hospital Affiliated to Shanghai University of Traditional Chinese Medicine (approval No. 2020-801-08-01) and registered at www.chictr.org.cn (ChiCTR2000038456).

